## 10.2 Serious Adverse Events (SAEs)

A Serious Adverse Event (SAE) is defined by the International Conference on Harmonization (ICH) guidelines and WHO GCP guidelines as any AE fulfilling at least one of the following criteria:

- Results in deaths.
- Life-threatening – defined as an event in which the subject was, in the judgment of the investigator, at risk of death at the time of the event; it does not refer to an event that hypothetically might have caused death had it been more severe.
- Requiring subject's hospitalization or prolongation of existing hospitalization – inpatient hospitalization refers to any inpatient admission, regardless of length of stay.
- Resulting in persistent or significant disability or incapacity (i.e., a substantial disruption of a person's ability to conduct normal life functions).
- Congenital anomaly or birth defect.
- Is medically significant or requires intervention to prevent at least one of the outcomes listed above.

Life-threatening refers to an event in which the subject was at risk of death at the time of the event.

It does not refer to an event that hypothetically might have caused death if it were more severe.

Important medical events that may not immediately result in death, be life-threatening, or require hospitalization may be considered as SAEs when, based upon appropriate medical judgment, they may jeopardize the subject and may require medical or surgical intervention to prevent one of the outcomes listed in the definitions above.

### 10.2.1 Hospitalization – Prolongation of existing hospitalization

Hospitalization is defined as an overnight stay in a hospital unit and/or emergency room.

An additional overnight stay defines a prolongation of existing hospitalization.

The following is not considered an SAE and should be reported as an AE only:

- Treatment on an emergency or outsubject basis for an event not fulfilling the definition of seriousness given above and not resulting in hospitalization.

The following reasons for hospitalizations are not considered AEs, and therefore not SAEs:

- Hospitalizations for cosmetic elective surgery, social and/or convenience reasons.
- Standard monitoring of a pre-existing disease or medical condition that did not worsen, e.g., hospitalization for coronary angiography in a subject with stable angina pectoris.
- Elective treatment of a pre-existing disease or medical condition that did not worsen, e.g., hospitalization for chemotherapy for cancer, elective hip replacement for arthritis.

#### **10.2.2 SAEs related to study-mandated procedures**

Such SAEs are defined as SAEs that appear to have a reasonable possibility of causal relationship (i.e., a relationship cannot be ruled out) to study-mandated procedures (excluding administration of study drug) such as discontinuation of subject's previous treatment during a washout period, or complication of a mandated invasive procedure (e.g., blood sampling, heart catheterization), or car accident on the way to the hospital for a study visit, etc.

#### **10.2.3 Suspected unexpected serious adverse reactions (SUSARs)**

SUSARs are all serious adverse reactions with suspect causal relationship to the study drug that is unexpected (not previously described in the SmPC - Summary of Product Characteristics or Investigator's brochure) and serious.

#### **10.2.4 Pregnancy**

Any pregnancy that occurs during study participation must be reported to the investigator/sponsor. To ensure subject safety, each pregnancy must be reported to the investigator/sponsor immediately. The pregnancy must be followed up to determine outcome (including premature termination) and status of mother and child. Pregnancy complications and elective terminations for medical reasons must be reported as an AE or SAE. Spontaneous abortions must be reported as an SAE.

Any SAE occurring in association with a pregnancy brought to the investigator's attention after the subject has completed the study and considered by the investigator as possibly related to the investigational product, must be promptly reported to the principal investigator/sponsor.

In addition, the investigator must attempt to collect pregnancy information on any female partners of male study subjects who become pregnant while the subject is enrolled in the study. Pregnancy information must be reported to the investigator/sponsor as described above.

### 10.3 Severity of adverse events

The severity of clinical AEs is graded on a three-point scale: mild, moderate, severe, and reported on specific AE pages of the CRF.

If the severity of an AE worsens during study drug administration, only the worst intensity should be reported on the AE page. If the AE lessens in intensity, no change in the severity is required.

If an AE occurs during a washout or placebo run-in phase and afterwards worsens during the treatment phase, a new AE page must be filled in with the intensity observed during study drug administration.

#### **Mild**

Event may be noticeable to subject; does not influence daily activities; the AE resolves spontaneously or may require minimal therapeutic intervention;

#### **Moderate**

Event may make subject uncomfortable; performance of daily activities may be influenced; intervention may be needed; the AE produces no sequelae.

#### **Severe**

Event may cause noticeable discomfort; usually interferes with daily activities; subject may not be able to continue in the study; the AE produces sequelae, which require prolonged therapeutic intervention.

A mild, moderate or severe AE may or may not be serious. These terms are used to describe the intensity of a specific event (as in mild, moderate, or severe myocardial infarction). However, a severe event may be of relatively minor medical significance (such as severe headache) and is not necessarily serious. For example, nausea lasting several hours may be rated as severe, but may not be clinically serious. Fever of 39°C that is not considered severe may become serious if it prolongs hospital discharge by a day. Seriousness rather than severity serves as a guide for defining regulatory reporting obligations.

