| EFFICACY ENDPOINTS                  | 
Primary:
 
 
• EVWL (measured with PiCCO® technique) until day 7 of treatment
 
 
Secondary:
 
 
• Oxygenation index (PaO2 / FiO2 ratio) until day 7 of treatment
 
• Ventilator plateau pressure until day 7 of treatment
 
• Murray Lung Injury Score until day 7 of treatment
 
• Ventilation parameters / lung function: tidal volume (Vt), positive endexpiratory pressure (PEEP), respiratory rate, FiO2, PIP, mean airway pressure, peak airway pressure until day 7 of treatment
 
• Duration of stay at ICU in the first 28 days
 
• Duration of controlled ventilation period until extubation
 
• Number of days free from ventilation support (for > 48 h) in the first 28 days
 
• Survival status at day 28
 
 |
| TOLERABILITY / SAFETY ENDPOINTS     | 
The local and systemic safety and tolerability and to identify possible dose related adverse events:
 
 
• Hemodynamic monitoring: heart rate (HR), systolic BP, mean arterial pressure (MAP), PBV, 24 hours fluid balance, CI and cardiac output (measured by PiCCO®) until day 7 of treatment
 
• Vital signs: pulse rate, and respiratory rate until day 7 of treatment
 
 
(Presence/absence/severity and duration of adverse effects – number and severity of adverse events (AEs), serious adverse events (SAEs) and suspected unexpected serious adverse events (SUSARs))
                                                                                                                                                                                                                                                                                                                                  |

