## **14. ETHICAL AND LEGAL ASPECTS**

### **14.1 Informed consent of subjects**

In this study it is expected that the vast majority of patients to be enrolled are temporarily unable to consent. For these patients (e.g. comatose patients), a subsequent informed consent has to be provided according to local law/ requirements.

In case a patient is able to consent, the patient must give written consent to participation in the study prior to embarking into any study related procedures, after they got comprehensive instructions regarding the nature, significance, impact and risks of this clinical trial. During the instruction regarding the clinical trial all trial participants are to be made aware of the fact that they can withdraw their consent – without giving reasons – at any time without their further medical care being influenced in any way.

In addition to the comprehensive instructions given to the trial participants by the investigator, the trial participants also receive a (if applicable: subsequent) written patient information sheet in comprehensible language, explaining the nature and purpose of the study and its progress.

The patients must agree to the possibility of study-related data being passed on to relevant authorities. The patients must be informed in detail of their obligations in relation to the trial participants insurance in order not to jeopardize insurance cover.

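### Section 10.3 separates moderate from severe adverse events by sequelae but also treats severity as intensity, so an intense, fully reversible event has two defensible grades; several anchors also cannot be scored under sedation.

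*Protocol*

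**What the plan says.** Under tolerability and safety endpoints, the synopsis (section 3) lists "number and severity of adverse events (AEs), serious adverse events (SAEs" together with SUSARs. Section 10.3 sets the scale: "The severity of clinical AEs is graded on a three-point scale: mild, moderate, severe". Section 10.5 makes severity a field of every adverse event record.

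The grade definitions in 10.3 read in part:

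- Mild: "Event may be noticeable to subject; does not influence daily activities". The event settles by itself or with little treatment.
- Moderate: the subject may be uncomfortable; "performance of daily activities may be influenced; intervention may be needed; the AE produces no sequelae".
- Severe: noticeable discomfort is possible, daily activities are usually affected, continuing in the study may not be possible, and "the AE produces sequelae, which require prolonged therapeutic intervention".

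The paragraph after these definitions says that the terms express how intense an event is. It names a severe headache as an event of little medical importance, and adds that "nausea lasting several hours may be rated as severe, but may not be clinically serious".

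On the population, section 8.1.2 requires intubation and mechanical ventilation. Section 9.4 expects examinations to take place under sedation. Section 14.1 expects that "the vast majority of patients to be enrolled are temporarily unable to consent".

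**The concern.** A severity scale should give one grade to one event, and it should rest on things the rater can see. Section 10.3 falls short on both counts.

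First, the line between moderate and severe is drawn by what the event leaves behind, while the accompanying text says the grades measure how strong the event is. These are different properties and can point to different grades.

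Second, each grade leans partly on what the subject notices or feels and on daily activities. A sedated, ventilated patient cannot report the first and has none of the second.

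At stake is a stated safety endpoint and the objective of local and systemic tolerability (section 7.2). Human experience so far is one single-dose study in 48 healthy men (section 6.3). This trial gives a dose every 12 hours for 7 days to critically ill patients (section 8). Acute, reversible events are plausible tolerability signals in that setting, and they fall on the unclear boundary.

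**Working it through.** No arithmetic applies, and the protocol gives no figure to reproduce. The check sets the parts of the protocol side by side.

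**1. Is the sequelae condition firm?** In the moderate and severe definitions most clauses are softened by may or usually. The two sequelae clauses are not: moderate has none, severe has them. Read literally, sequelae are required for severe and excluded from moderate.

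**2. Apply both readings to one case.** Take an intense event that needs substantial treatment and resolves completely.
- By the definitions it is not severe, because there are no sequelae. It fits moderate, which allows for intervention.
- By the explanatory text it can be severe, because intensity decides. Hours of nausea or a headache do not imply sequelae, yet both are offered as possible severe events.

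The same event therefore has two defensible grades.

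**3. Apply them to the converse case.** An event of modest intensity that leaves sequelae needing long treatment is excluded from moderate and meets the sequelae clause of severe. An event with sequelae that do not need long treatment fits neither definition fully. The wording can thus displace grades in more than one direction.

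**4. Can the deciding fact be known?** Section 11.1 requires follow-up to resolution or stabilisation only for SAEs. For a non-serious event, whether sequelae followed may never be established. The outcome list in section 10.5 has four entries (resolved, ongoing, ongoing and improved, ongoing and worsening), and none of them records sequelae. Section 10.3 also asks for the worst intensity to be reported, which again assumes that the grade measures intensity.

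**5. Which anchors can be scored under sedation?**

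| Anchor | Mild | Moderate | Severe | Scorable under sedation |
|---|---|---|---|---|
| Perception or comfort | yes | yes | yes | no |
| Daily activities | yes | yes | yes | no |
| Degree of intervention | yes | yes | yes | yes |
| Ability to continue in the study | – | – | yes | yes |
| Sequelae | – | yes | yes | only later |

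Degree of intervention and ability to continue remain usable. The wording for intervention at moderate and for continuation at severe is permissive, so neither overrides the firm sequelae clauses.

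**The case against.** The strongest reply is that the scale still works. Degree of intervention runs through all three grades, and ability to continue is observable, so sequelae are not the only anchor left in a sedated patient. The perception clauses are permissive, and section 10.3 uses myocardial infarction as an example of an event graded by intensity, which needs no report from the patient. All of this stands. It narrows the point to the conflict between definitions and examples and to the poor fit of some anchors. It does not resolve that conflict.

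The reply also says that little depends on the grade. Seriousness, not severity, guides regulatory reporting (10.3), and the seriousness criteria in 10.2 cover life-threatening and medically significant events. Haemodynamic and ventilation values are recorded daily (9.5.6). Grading is blinded and follows the same rule in both arms (9.3). The summary in 12.6.3 names no tabulation by severity. This limits the consequence, but severity remains a listed endpoint, and misgrading that is alike in both arms tends to dilute a real difference.

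A reader might infer three stronger things that the protocol does not support:

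- That severity is certainly under-graded. The direction is an inference, because raters may follow the definition or the examples.
- That nearly all patients cannot be graded throughout. Section 14.1 concerns temporary incapacity to consent. Section 9.4 foresees conscious patients and 9.5.3 foresees extubation during treatment. Adverse events are collected up to the telephone interview on day 28 (+7) (9.5.4). The difficulty applies while the patient is sedated.
- That rewording would lose comparability with phase I. Table 2 gives counts of possibly related events by dose and contains no severity grades.

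**Conclusion.** The point holds as a contradiction within section 10.3 that leaves the moderate/severe boundary open, with a secondary problem of anchors that do not suit sedated patients. The contradiction needs no assumption about sedation. It rests on reading the nausea and headache examples as events without sequelae, which is the natural reading although the protocol does not say so. The secondary problem rests on the sedation expected in section 9.4 and lasts only as long as the sedation does.

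The size is qualitative. The events affected are intense but reversible ones, whose severity may be under-graded or graded inconsistently. The protocol does not allow a count of patients or events. It is a modest point, worth correcting because it changes how a stated safety endpoint is scored and the correction is cheap.

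**What to change.** Change section 10.3 and the eCRF completion guidance as follows.

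- Delete the sequelae condition from moderate and severe, so that severity grades intensity only and agrees with the section's own examples.
- Add anchors that can be observed in a sedated patient, for example the degree of change in monitored findings or the degree of intervention needed. Keep them distinct from the seriousness criteria in 10.2, so that severe does not become another word for serious.
- Keep the wording on perception, comfort and daily activities for patients who are awake.
- Add a category for sequelae to the adverse event outcome list in 10.5, since removing them from the grade would otherwise leave that list with no place for them.

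The cost is a small change to the eCRF and to investigator guidance. No new assessments or patients are needed.

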## 10.4 Relationship to study drug

For all AEs, the investigator will assess the causal relationship between the study drug and the AE using his/her clinical expertise and judgment according to the following algorithm that best fits the circumstances of the AE:

|   |                    |                                                                                                                                                                                                                                                                                                                                                                                                                                  |
|---|--------------------|----------------------------------------------------------------------------------------------------------------------------------------------------------------------------------------------------------------------------------------------------------------------------------------------------------------------------------------------------------------------------------------------------------------------------------|
| 1 | NOT RELATED | This category applies to those adverse events which, after careful consideration, are clearly and incontrovertibly due to extraneous cause (disease, environment, etc.).                                                                                                                                                                                                                                                         |
| 2 | UNLIKELY    | A clinical event, including laboratory test abnormality, with a temporal relationship to drug administration that makes a causal relationship improbable, and in which other drugs, chemicals, or underlying disease provide plausible explanations.                                                                                                                                                                             |
| 3 | POSSIBLY    | A clinical event, including laboratory test abnormality, with a reasonable time sequence to administration of the drug, but which could also be explained by concurrent disease or other drugs or chemicals. Information on drug withdrawal may be lacking or unclear.                                                                                                                                                           |
| 4 | PROBABLY    | A clinical event, including laboratory test abnormality, with a reasonable time sequence to administration of the drug, unlikely to be attributed to concurrent disease or other drugs or chemicals, and which follows a clinically reasonable response on withdrawal (dechallenge). Rechallenge information is not required to fulfil this definition.                                                                          |
| 5 | DEFINITELY  | A clinical event, including laboratory test abnormality, occurring in a plausible time relationship to drug administration, and which cannot be explained by concurrent disease or other drugs or chemicals. The response to withdrawal of the drug (dechallenge) should be clinically plausible. The event must be definitive pharmacologically or phenomenologically, using a satisfactory rechallenge procedure if necessary. |

## 10.5 Reporting procedures

A special section is designated to adverse events in the case report form. The following details must thereby be entered:

- Type of adverse event

- Start (date and time)
- End (date and time)
- Severity (mild, moderate, severe)
- Serious (no / yes)
- Unexpected (no / yes)
- Outcome (resolved, ongoing, ongoing – improved, ongoing – worsening)
- Relation to study drug (not related, unlikely, possibly, probably, definitely))

Adverse events are to be documented in the case report form in accordance with the above mentioned criteria.

#### 10.5.1 Reporting procedures for SAEs

All unexpected SAEs must be reported to the KKS by FAX or email within 24 hours of learning of the occurrence using the SAE Case Report Form.

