### 10.1.2 Definition of adverse events

An AE is any untoward adverse change from the subject's baseline condition, i.e., any unfavorable and unintended sign including an abnormal laboratory finding, symptom or disease which is considered to be clinically relevant by the physician that occurs during the course of the study, whether or not considered related to the study drug.

Adverse events include:

- Exacerbation of a pre-existing disease.
- Increase in frequency or intensity of a pre-existing episodic disease or medical condition.
- Disease or medical condition detected or diagnosed after study drug administration even though it may have been present prior to the start of the study.
- Continuous persistent disease or symptoms present at baseline that worsen following the start of the study.
- Lack of efficacy in the acute treatment of a life-threatening disease.
- Events considered by the investigator to be related to study-mandated procedures.
- Abnormal assessments, e.g., ECG and physical examination findings, must be reported as AEs if they represent a clinically significant finding that was not present at baseline or worsened during the course of the study.
- If laboratory test abnormalities are evaluated as an AE remains to the discretion of the investigator.

Adverse events do not include:

- Pre-planned interventions or occurrence of endpoints specified in the study protocol are not considered AE's, if not defined otherwise (eg.as a result of overdose)
- Medical or surgical procedure, e.g., surgery, endoscopy, tooth extraction, transfusion. However, the event leading to the procedure is an AE. If this event is serious, the procedure must be described in the SAE narrative.

- Pre-existing disease or medical condition that does not worsen.
- Situations in which an adverse change did not occur, e.g., hospitalizations for cosmetic elective surgery or for social and/or convenience reasons.
- Overdose of either study drug or concomitant medication without any signs or symptoms. However, overdose must be mentioned in the Study Drug Log.

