#### **10.5.4 Safety Monitoring Board**

A Safety Monitoring Board will be installed for the case of safety concerns and the need of decisions regarding the study progress made by the Sponsor.

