### 12.6.2 Secondary endpoint analysis

Secondary efficacy variables are:

1. the treatment associated changes of oxygenation as measured by the  $\text{PaO}_2$  /  $\text{FiO}_2$  ratio until day 7 of therapy,
2. the ventilatory plateau pressure until day 7 of therapy,
3. the Murray lung injury score (a composite variable that includes components of oxygenation, compliance, positive end-expiratory pressure, and the appearance of the chest radiograph),
4. ventilation parameters: tidal volume ( $V_t$ ), positive endexpiratory pressure (PEEP), respiratory rate,  $\text{FiO}_2$ , PIP, mean airway pressure, peak airway pressure until day 7 of treatment
5. the duration of stay at ICU in the first 28 days,
6. the duration of controlled ventilation period until extubation,
7. the number of days free from ventilatory support [for > 48 h] in the first 28 days,
8. the survival status at day 28,
9. the local and systemic safety and tolerability and to identify possible dose related adverse events.

Secondary efficacy variables will be presented using appropriate descriptive methods, and will be analysed in an explorative sense: Mann-Whitney U-Test (Variable 1, 2, 3, 4), Kaplan-Meier estimates (variable 5, 6, 7, 8), and contingency tables (variable 9)

Statistical tests of the secondary efficacy variables and the p-values attached to them will be regarded as descriptive and not as tests of hypotheses.

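### The protocol leaves open whether a death is an SAE, sets a 24-hour limit only for unexpected SAEs, and has no fatal outcome code on the AE page

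*Protocol*

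**What the plan says.** Five provisions of the protocol bear on this point.

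- **Section 10.1.2, what is not an AE:** "occurrence of endpoints specified in the study protocol are not considered AE's, if not defined otherwise". The only example given for the exception is overdose. The same section counts as an AE: "Lack of efficacy in the acute treatment of a life-threatening disease".
- **Section 10.2, SAE definition:** an SAE is "any AE fulfilling at least one of the following criteria", and death is the first criterion listed.
- **Synopsis and section 12.6.2, endpoints:** "the survival status at day 28" is a secondary efficacy variable.
- **Sections 10.5 and 10.5.1, recording and reporting:** the AE page must carry "Outcome (resolved, ongoing, ongoing – improved, ongoing – worsening" and a yes/no entry for unexpected. The time limit reads: "All unexpected SAEs must be reported to the KKS by FAX or email within 24 hours of learning of the occurrence". Beyond that, 10.5.1 foresees only a periodic summary to authorities and ethics committees on a yearly scale. Section 10.5.3 adds an annual safety report.
- **Section 10.5.4, board:** "A Safety Monitoring Board will be installed for the case of safety concerns". No date of constitution, schedule or trigger follows.

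**The concern.** These rules do not fit together for the most important safety event in an intensive care trial. One investigator, following 10.2, files a death as an SAE. Another, following 10.1.2, records it only as survival status, which 9.5.4 collects at the day 28 (+7) telephone interview. Even when a death is filed as an SAE, the 24-hour limit depends on a yes/no entry for which no reference is named. On the AE page a fatal event can be entered only under a wrong or empty outcome.

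Section 8.1.7 requires the trial to stop if adverse events make the balance of risk and benefit unacceptable. That rule works only if deaths and other SAEs reach the people who apply it, in good time and under one definition. Earlier human exposure was to single doses in 48 healthy men, 12 of them on placebo (section 6.3 and Table 2). This trial gives repeated inhalations for 7 days to ventilated patients.

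**Working it through.** The protocol gives no figure to reproduce. The check is a side-by-side reading, followed by simple arithmetic for scale.

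**Step 1: is a death an SAE?**

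- Premise a (10.2): every SAE is an AE.
- Premise b (10.1.2): an endpoint occurrence is not an AE, unless defined otherwise.
- Premise c (synopsis, 12.6.2): survival at day 28 is an endpoint.
- Reading A: a death is an occurrence of the survival endpoint. By b it is not an AE, and by a it is not an SAE.
- Reading B: the death criterion in 10.2 is itself the definition otherwise, so a death is an SAE. The lack-of-efficacy item in 10.1.2 points the same way.

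Both readings can be defended from the text, and no sentence decides between them.

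**Step 2: when does an SAE reach the KKS?**

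| Type of SAE | Stated time limit |
|---|---|
| Unexpected | 24 hours (10.5.1) |
| Not unexpected | none; periodic summary (10.5.1) and annual report (10.5.3) |

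The synopsis gives a study period of 1 year, so a yearly summary could first appear as the trial is ending.

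Which row applies depends on how expectedness is judged:

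- Against the brochure or SmPC, as 10.2.3 says for SUSARs: phase I had no SAE (6.3, 10.1.1), so many SAEs could count as unexpected and go within 24 hours.
- Against the underlying disease: most ICU deaths could be ticked as expected and have no deadline.

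The brochure is not at hand, and 10.5.1 does not say which standard holds.

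**Step 3: can the AE page code a death?** The list in 10.5 has four outcomes: one resolved and three ongoing. None is fatal.

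**Step 4: how often would this arise?**

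Inputs: N = 40, 20 per group (12.2); cited mortality 30% to 60% (6.1), a general ALI/ARDS figure with no time horizon stated.

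- Expected deaths = N × mortality: 40 × 0.30 = 12 and 40 × 0.60 = 24.
- Per arm, if the arms are alike: 20 × 0.30 = 6 and 20 × 0.60 = 12.
- Probability of at least 6 deaths among 40 (binomial): 0.991 at 30% and above 0.999 at 60%.

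**The case against.** The strongest reply is that deaths and SAEs are captured by several other routes.

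- Section 10.2 names death first, and the exclusion in 10.1.2 carries its own exception.
- The endpoint is a status at day 28, not an event.
- The AE page has a serious yes/no field. Section 11.1 follows up all SAEs, and 13.3.1 requires full verification of SAE documentation. Section 9.5.4 documents survival.
- The SAE form asks for the outcome (10.5.1), and SUSAR reports list death (10.5.2).

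All of this stands. A reader might infer that deaths and expected SAEs escape safety capture altogether, and the documents do not support that. Three further inferences also go beyond the text:

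- *Every expected ICU death misses the 24-hour route.* This holds only if expectedness is judged against the disease, which the protocol does not say.
- *The AE tables would misreport fatal events.* Section 12.6.3 tabulates AEs by group, system organ class, MedDRA term and phase, not by outcome. The gap is on the AE page.
- *The board exists only after a concern is raised, so an imbalance between arms must stay unseen.* The wording in 10.5.4 equally allows a board set up in advance. The code-break envelope in 9.3.1 lets an investigator learn a single patient's treatment after a serious event, though this gives no comparison of arms.

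The mortality range may also be too high here. The trial excludes septic shock and immunosuppression and requires 8 stable hours on ventilation.

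None of these replies settles whether a death is an AE, supplies a deadline for the remaining SAEs, names the reference for expectedness or adds a fatal code.

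**Conclusion.** The point holds as an inconsistency in how deaths and SAEs are defined, timed and coded. Sections 10.1.2 and 10.2 conflict on deaths. Section 10.5.1 sets a time limit for one class of SAE only and does not define that class. Section 10.5 cannot code a fatal outcome. Section 10.5.4 is ambiguous about when the board is formed.

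On the cited mortality, 12 to 24 deaths among 40 patients would meet these rules. This assumes that a general ALI/ARDS rate carries over to a selected population. With a lower rate the count falls, but the contradiction remains. The consequence shown is possible delay and inconsistent recording. The documents do not show that deaths would be lost.

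**What to change.** 1. **Section 10.1.2:** state that deaths are recorded and reported as SAEs even when they are also endpoints, so that it agrees with 10.2.
2. **Section 10.5.1:** delete the word *unexpected*, so that all SAEs go to the KKS within 24 hours. At minimum, require this for all deaths and name the document against which expectedness is judged.
3. **Section 10.5 and the eCRF:** add a fatal category to the outcome list.
4. **Section 10.5.4:** state that the board already foreseen is constituted before enrolment. A schedule of safety reviews by arm is optional; nothing in the protocol is contradicted by its absence.

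The cost is more SAE forms for the site and small changes to the eCRF and the protocol wording. Sample size and the primary analysis are untouched.
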